**Figure 1 F1:**
[figure not shown]
Phototherapy and exchange transfusion thresholds for neonates with a gestational age of 35 weeks or more. Translated from Dutch. The Dutch nomogram can be downloaded from the website (http://babyzietgeel.nl/kinderarts/hulpmiddelen/diagnostiek/bilicurve35wkn.php). AS, Apgar score; ET, exchange transfusion; PT, phototherapy; TSB, total serum bilirubin.

#### Intervention 2: phototherapy in the PCBC

During this study phase, the default location for application of phototherapy, if clinically indicated, will be the PCBC, rather than the hospital. The indication for phototherapy is made by a paediatrician in the affiliated hospital based on the TSB level, according to the Dutch nomogram.^9^ Phototherapy in the PCBC will be provided using GE Healthcare BiliSoft Large, a commercially available, CE-marked and validated phototherapy mattress using blue LED-light.^33^ This phototherapy mattress is suitable for application in primary care as well as in the hospital setting.

The affiliated paediatrician will decide whether other blood tests have to be performed to determine the cause of hyperbilirubinaemia and at what time points follow-up TSB measurements need to be taken. Based on the results of these TSB measurements (dis)continuation of phototherapy and further follow-up is determined by the affiliated paediatrician. The affiliated paediatrician may decide to admit a neonate to the hospital for further hyperbilirubinaemia treatment at any time if there are strong reasons to do so; these reasons will be recorded. Phototherapy will not be applied in the PCBC in neonates who have hyperbilirubinaemia above the phototherapy threshold within 24 hours after birth, since this is considered to represent a likely pathological cause of hyperbilirubinaemia and bilirubin levels may rise swiftly in these neonates.^9^

Each PCBC will start with a time period without any intervention (control period), followed by a time period with only one of the interventions, and then a time period with both interventions. The inclusion of neonates will take 2.5 years per PCBC. The sequence and the timing at which the PCBC will switch over to the next intervention period will be determined by random allocation. The allocation scheme with the possible sequences of the interventions is depicted in figure 2. The time blocks will take 4 months, except for the first and the last block. These two blocks will cover 5.5 months, because, to be able to make a comparison within a cluster, a sufficient number of participants in the control period (C) and in the period with both interventions (I1 + I2) should be included, even when a smaller PCBC is randomised to time line 1 or 6.

**Figure 2 F2:**
[figure not shown]
Allocation scheme. C, control; I1, intervention 1, transcutaneous bilirubinometry measurement; I2, intervention 2, phototherapy in primary care birth centres.

A flowchart with an overview of the study procedures with the different intervention phases and possible orders of intervention phases from the perspective of a participant is displayed in figure 3.

**Figure 3 F3:**
[figure not shown]
Flowchart for study inclusion. GA, gestational age; TcB, transcutaneous bilirubinometry; TSB, total serum bilirubin; PCBC, primary care birth centres.

### Primary outcomes

The two interventions each have their own primary outcome. The primary outcome for TcB measurement as a screening tool for jaundice will be the proportion of neonates having severe hyperbilirubinaemia at any time point within the first 14 days of life. Severe hyperbilirubinaemia is defined as a TSB level above the mean of the phototherapy and exchange transfusion thresholds, according to the Dutch nomogram^9^;that is,

$$TSB>\frac{phototherapy\;threshold+exchange\;transfusion\;threshold}{2}$$

For the second intervention, phototherapy in the PCBC, the primary outcome will be the proportion of neonates requiring hospital admission for hyperbilirubinaemia treatment within the first 14 days of life. Hyperbilirubinaemia treatment will be considered the indication for hospital admission if the neonate received phototherapy or an exchange transfusion for hyperbilirubinaemia within 24 hours after hospital admission.

### Secondary outcomes

The secondary outcomes will also be assessed within the first 14 days of life (except for kernicterus) and are listed in table 1.

**Table 1 T1:** Secondary outcomes

Secondary outcomes		
Assessed in	Outcome	Recorded by
All neonates	Number of times TcB quantified	Maternity care professional
	Individual TcB readings	Maternity care professional
	Highest TSB level	Maternity care professional and/or EMR in hospital
	Number of neonates having TSB quantified	Maternity care professional
	Number of times blood taken for TSB quantification	Maternity care professional and/or EMR in hospital
	Individual TSB levels	Maternity care professional and/or EMR in hospital
	Number of times blood taken for TSB quantification before start of phototherapy	Maternity care professional and/or EMR in hospital
	Number of neonates receiving phototherapy	Maternity care professional and/or EMR in hospital
	Duration (hours) of phototherapy	Maternity care professional and/or EMR in hospital
	Number of neonates having TSB level above exchange transfusion threshold^9^	Maternity care professional and/or EMR in hospital
	Number of neonates who actually received an exchange transfusion	EMR in hospital
	Number of neonates having kernicterus*	EMR in hospital and/or EMR at general practitioner
	Duration of stay in the PCBC	Maternity care professional
	Duration of hospital stay following initial PCBC admission (if relevant)	EMR in hospital
	Number of transfers between PCBCs/hospitals	Maternity care professional and parental questionnaire
	Number of times affiliated paediatrician consulted	Maternity care professional
	Experience of parents regarding hyperbilirubinaemia assessment and treatment	Parental questionnaire
	Experience of attending maternity care personnel regarding the daily practice of hyperbilirubinaemia assessment and treatment during control and intervention periods, including facilitators and barriers for implementation	Maternity care assistant questionnaire
Within the group included in the intervention period with phototherapy in the PCBC	The number of neonates in whom phototherapy was initiated in the hospital, including reasons for this hospital admission	EMR in hospital
	The number of neonates requiring subsequent hospital admission for hyperbilirubinaemia treatment (ie, after initiation of phototherapy in the PCBC), including reasons for this ’treatment failure'	EMR in hospital

*The diagnosis of kernicterus will be made by combining clinical signs and symptoms and additional investigations (eg, cerebral ultrasound, MRI) up to 1 year after birth in every neonate who had a TSB level above the exchange transfusion threshold level.

EMR, electronic  medical record; PCBC, primary care birth centres; TcB, transcutaneous bilirubinometry; TSB, total serum bilirubin.

### Cost-effectiveness analysis

A cost-effectiveness analysis (CEA) will be performed from the healthcare perspective. In the CEA, the costs and outcomes of the interventions, compared with ’usual care', will be identified, measured and valued.

For all of the following items, healthcare use will be measured: TSB and TcB tests, phototherapy in the hospital, phototherapy in the PCBC, exchange transfusions, PCBC and/or hospital admission days and ambulance transportation to a hospital. These data will be recorded during the study and/or retrieved from the electronic information systems of the participating PCBCs and affiliated hospitals.

Then, integral unit prices will be calculated using real economic cost prices or using standard cost-prices for health economic evaluations.^34^ Unit prices will be multiplied by the quantities for each resource used and summed over the separate types of resources to give the total cost per patient.

Regarding the outcomes, the CEA will look at the number of neonates with severe hyperbilirubinaemia (as defined above) and the number of hospital admissions. Data on costs and outcomes will be measured throughout the 14-day observation period. As the final outcome measure of the CEA, incremental cost effectiveness ratios (ICERs) will calculated, expressed as incremental costs per case of severe hyperbilirubinaemia or hospitalisation avoided. Uncertainty in the estimation of the ICERs will be illustrated through cost-effectiveness planes. Where relevant, sensitivity analyses will be performed to assess the robustness of the analyses to certain assumptions.

### Sample size

Two sample size calculations are required since two interventions, each with their own outcomes, are evaluated. The interventions are considered to be independent of each other and therefore the larger sample size among the two sample size calculations is considered appropriate for the entire study. Sample size calculations are based on detecting superiority rather than non-inferiority.

The estimated incidence of severe hyperbilirubinaemia in term neonates in the Netherlands is 1.2% per year.^9^ A previous study in Canada regarding screening for unconjugated hyperbilirubinaemia using TcB among healthy neonates with ≥35 weeks of gestation showed a relative reduction of 55% in severe hyperbilirubinaemia following implementation.^16^ We therefore hypothesise that the TcB screening intervention will decrease the incidence of severe hyperbilirubinaemia from 1.2% to 0.5% (ie, by 0.7% points; a relative reduction of 58%). At a power of 80% and a two-sided alpha of 0.05, 2691 neonates per arm are needed to identify this effect.

The estimated proportion of neonates needing phototherapy is 4%.^9^ We anticipate that approximately 50% of the neonates with hyperbilirubinaemia will have an indication to be admitted to the hospital (eg, feeding difficulties in addition to hyperbilirubinaemia or need for intensive phototherapy). Therefore, we hypothesise that the planned application of phototherapy in the PCBC will decrease the need for hospital admission for hyperbilirubinaemia by 2% points (ie, 50% relative reduction). At a power of 80% and a two-sided alpha of 0.05, 1136 neonates per arm are needed to identify this effect. While our study is a cluster RCT, given the cross-sectional nature of a stepped-wedge design the effect of intracluster correlation on power is minimal, therefore we did not adjust for intracluster correlation.^35^

Based on the larger sample size of 2691 neonates per arm, 5382 neonates are needed in total. We aim to include 5500 neonates to account for a degree of missing data.

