### Statistical analysis

We will use cluster-specific methods because randomisation will be performed at the PCBC level rather than at the individual level. For both primary objectives, an intention-to-treat analysis will be performed.

To evaluate whether the occurrence of the primary outcomes of both interventions are different between the study periods with and without the intervention(s), generalised linear mixed models (GLMMs) will be used. GLMMs account for the systematically different observation periods and for clustering in the data.^36^ In case of missing data, multiple imputation using chained equations will be used. Relative risks, risk differences, and relative risk reduction with corresponding 95% CIs will be calculated from the GLMMs.

Subgroup analyses to evaluate the effect of the interventions in neonates of different ethnicities (Caucasian and non-Caucasian) and different GA groups (<38 weeks of gestation and ≥38 weeks of gestation) will be performed.

We will perform a per-protocol analysis to assess the impact of potential contamination during the first days of a new intervention period as a sensitivity analysis in addition to the intention-to-treat analysis.

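### The 80% power for the TcB outcome is that of an individually randomised two-arm trial; under the planned period-adjusted stepped-wedge analysis, 5500 neonates give clearly less

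*Protocol article*

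**What the plan says.** Under Sample size, the Protocol article takes 1.2% as the usual-care risk of severe hyperbilirubinaemia and assumes TcB screening lowers it to 0.5%, a 58% relative reduction. It concludes: "At a power of 80% and a two-sided alpha of 0.05, 2691 neonates per arm are needed to identify this effect". For hospital admission (4% to 2%): "At a power of 80% and a two-sided alpha of 0.05, 1136 neonates per arm are needed to identify this effect". The larger figure sets the trial: "Based on the larger sample size of 2691 neonates per arm, 5382 neonates are needed in total", raised to 5500 for missing data. The only remark on design is that, for a cross-sectional stepped-wedge, "the effect of intracluster correlation on power is minimal, therefore we did not adjust for intracluster correlation".

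Elsewhere the article fixes a different design and analysis:

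- **Study sites:** six clusters (five single centres and one pair).
- **Intervention 2 (allocation scheme):** each cluster starts with usual care, moves to one intervention and ends with both. "The time blocks will take 4 months, except for the first and the last block"; those two last 5.5 months each.
- **Statistical analysis:** "GLMMs account for the systematically different observation periods and for clustering in the data".

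**The concern.** The sample size treats the trial as two independent groups of about 2750, with exposure unrelated to calendar time, centre or the other intervention. In the actual design exposure is tied to calendar time: nobody has TcB screening in the first block and everybody has it in the last. Once the model adjusts for period, those blocks no longer inform the TcB effect. The reason given for making no adjustment speaks only of intracluster correlation and leaves this loss out.

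The TcB outcome determines the size of the whole trial. If it shows no significant effect, readers will take that as evidence from a trial with an 80% chance of finding a 58% reduction. If the true chance is nearer one half or less, the result is much weaker evidence against screening than it will appear.

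**Working it through.** **1. Reproducing the stated figures.** Inputs (Sample size): 1.2% vs 0.5%, two-sided alpha 0.05, power 80%.

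n per arm = (1.960 + 0.842)² × (0.012×0.988 + 0.005×0.995) / 0.007² = 7.849 × 0.016831 / 0.000049 = 2696 (2699 with pooled variance). Stated: 2691, within 0.3%. For 4% vs 2%: 7.849 × 0.0580 / 0.0004 = 1138. Stated: 1136. Both are individually randomised two-arm figures. At 2750 per arm the same formula gives about 81% power for TcB.

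**2. Ceiling with period adjustment and ICC = 0.** Figure 2 is not shown. Blocks of 5.5 + 5×4 + 5.5 months give 31 months, close to the stated 2.5 years. With period as a categorical factor, only within-block comparisons count. If a share p_j of neonates in block j has TcB, and block j holds a share w_j of all neonates, then relative to a balanced two-arm trial

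variance inflation = 1 / Σ w_j × 4p_j(1 − p_j).

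The first block (p = 0) and last block (p = 1) contribute nothing; together they are 11 of 31 months. With the clusters split 3:3 in every middle block, the inflation is 31/20 = 1.55. The effective number per arm is 2750/1.55 = 1774, and

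power = Φ(0.007/√(0.016831/1774) − 1.960) = Φ(0.313) = 62%.

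Using 19 of 30 months gives 61%. A 4:2 split or favourable unequal cluster sizes gives up to 63.5%. A linear time term in place of categorical periods gives about 70% at best.

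**3. A layout that fits the text, ICC = 0.** Let one further cluster start TcB at each of the six switches, so the middle blocks have 1, 2, 3, 4 and 5 of six clusters on TcB. Then Σ = (4/31) × 4 × (5+8+9+8+5)/36 = 0.502 and the inflation is 1.99. With the second intervention also in the model it is 2.01, and power is about 51%. As a cross-check, the Woertman design effect (equal blocks, one intervention) is 1.80, power 56%. Of some 15,000 randomly drawn layouts, those that fit the text had median power of 45-49%, depending on whether the other intervention is in the model.

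**4. Adding intracluster correlation (assumed; the article gives none).** Generalised least squares with a random cluster effect, categorical periods, equal clusters and 5500 neonates:

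| ICC | Layout of step 3, both interventions in model: inflation, power | Sampled layouts: median power (maximum) | Woertman: design effect, power |
|---|---|---|---|
| 0 | 2.01, 51% | 45-49% (63.5%) | 1.80, 56% |
| 0.001 | 2.51, 43% | 39-42% (50%) | 2.26, 47% |
| 0.005 | 3.08, 36% | 34-37% (41%) | 2.76, 40% |

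Simulating a period-adjusted logistic model for the step 3 layout gave 50-52% with no centre variation, and 35-39% with a centre SD of 0.3 on the logit scale and centre effects fitted.

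**5. Detectable reduction at 5500, 80% power, 1.2% under usual care.** Solving the power formula for the lower risk:

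- inflation 1.55: 0.37%, a 69% reduction
- inflation 2: 0.28%, a 76% reduction
- inflation 3: 0.14%, an 89% reduction

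**6. Admission outcome.** It needs 1138 per arm and has 2750, so 80% power survives any inflation up to 2750/1138 = 2.42. Power is 90%, 79% and 71% at design effects of 1.8, 2.5 and 3. Which design effect applies depends on figure 2.

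**The case against.** **The ceiling is conditional.** The article does not say how time enters the model, never states the number of blocks, and its allocation figure is not available here. This stands. A reader might infer that power cannot exceed 62%; the documents do not support so flat a limit. Favourable splits reach 63.5% and linear time about 70%. Only dropping the period adjustment comes close to the stated power (79% in the best layout tried, at ICC = 0). That would contradict the Statistical analysis section and leave the effect confounded with calendar time.

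**The correlations are assumed, and the upper ones are large for a rare outcome.** At a mean risk of 0.85%, an ICC of 0.005 implies a between-centre SD of √(0.005 × 0.0085 × 0.9915) = 0.65 percentage points, a coefficient of variation of 0.76. At 0.01 it is 1.08, an SD above the mean. This stands, and it is why the range here ends at 0.005. At 0.001 the coefficient is 0.34, and power still falls by several points.

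**The sentence on intracluster correlation is not the main error.** This is largely right. Most of the loss comes from period adjustment, and once some correlation is present, power changes slowly: median 39-42% at 0.001 and 33-35% at 0.01. Deleting the sentence alone would not correct the power. But the step from 0 to 0.005 costs about 11-15 points (step 4), which is not minimal.

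**Other readings that go too far.** A reader might infer an arithmetic slip; there is none, since 2691 is right for the design it assumes. A reader might infer that only near-elimination of severe hyperbilirubinaemia is detectable; 69-76% is the figure before clustering, and 89% needs an inflation of 3. A reader might infer that the admission outcome fails equally; it has more than twice the neonates its formula requires.

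**Conclusion.** The stated 80% power for the TcB outcome does not hold for the trial as designed and analysed. With 5500 neonates and categorical period effects it is at most about 62-64% (about 70% with linear time), about 40-50% in typical layouts, and roughly 30-45% with an ICC of 0.001-0.005. Falling short of 80% does not depend on the ICC or on the exact allocation scheme, provided period is adjusted for; the exact value depends on both.

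Assumptions not in the documents are seven blocks, equal cluster sizes, the layouts, the ICC values and the coding of time. Permuting unequal cluster sizes moved power by up to about 9 points at ICC = 0. Normal-based tests with six clusters are, if anything, optimistic. This is not a detail that a later analysis plan can settle, because the article states both the power figure and a reason for not adjusting it.

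**What to change.** In the Sample size section:

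1. Remove the statement that intracluster correlation has minimal effect on power.
2. Recompute power for both primary outcomes from the actual figure 2 scheme: six clusters, planned block lengths, and period, cluster and both intervention terms in the model. Use a stated ICC range plausible for an outcome of about 1%, for example 0-0.005.
3. Replace the 80% claim with the result, and give the reduction detectable with 80% power at 5500 neonates for each outcome.

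The cost is a short calculation and a change of wording, with no change to enrolment or conduct. The downside is a less favourable stated power for the TcB question.

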### Randomisation and blinding

Each of the participating PCBCs will be randomised to one of the predefined timelines (as depicted in figure 2 above) by an online randomisation module (www.randomization.com). The two smallest PCBCs will be paired and randomised to the same timeline (see figure 2).

Given the nature of the treatment in the intervention groups and the control group, blinding of participants (and parents) and healthcare personnel is not possible. Analyses will be performed by a researcher who is blinded to the PCBC allocation scheme.

### Study procedures

All PCBCs in the Netherlands that provide maternity care to mothers and neonates in the first days after delivery were invited to participate. Eligibility of neonates admitted to the PCBC will be assessed by the maternity care or study personnel based on the inclusion and exclusion criteria. IC of parents will be obtained by the maternity care professional. Research nurses and study personnel will support the maternity care professionals in obtaining IC and collecting data.

Depending on the allocation and the moment of admission in the PCBC during the study period, the neonate is included in the control period, in a time period where one of the interventions is implemented, or in a time period where both interventions are implemented. Standard operating procedures (SOPs) for each study phase have been developed.

Maternity care personnel of all PCBCs will be trained in the SOPs and in using the transcutaneous bilirubinometer and the phototherapy mattress to ensure the interventions are applied in a professional standardised manner. For this purpose, an e-learning module has been developed (available from: https://xoteur.12change.eu/play.php?template_id=798); in addition, during the study period three training sessions for maternity care professionals are held at each PCBC prior to the start of each subsequent study phase (ie, intervention implementation).

### Data collection

Data collection at the PCBC will be performed by maternity care personnel. Together with the training for using the transcutaneous bilirubinometer and the phototherapy mattress, maternity care personnel will be trained in adequate data collection. Data collection is described in the SOPs as well.

After inclusion, a maternity care professional of the PCBC will record baseline characteristics of the mother and the neonate (see table 2) using a standardised registration form at a secured internet page. All participants will receive an anonymised study number.

**Table 2 T2:** Baseline characteristics

Baseline characteristics	
Parental characteristics	Maternal age
	Maternal ethnicity
	Maternal blood group
	Paternal ethnicity
	Presence of haemolytic disease (other than blood group antagonism) in mother or father
Characteristics of pregnancy and birth	Parity
	Maternal atypical red-cell alloantibodies during pregnancy
	Gestational age at birth
	Type of delivery: vaginal delivery, vacuum-assisted vaginal delivery, forceps-assisted vaginal delivery, caesarean delivery without vacuum or forceps extraction (before or during delivery), caesarean delivery with vacuum or forceps extraction (before or during delivery).
Neonatal characteristics	Date of birth
	Time of birth
	Sex
	Birth weight (in grams)
	Presence of birth trauma
	Type of feeding
	Neonatal blood group (if known)
	Foetal or neonatal Rhesus factor (if known)
	Direct antiglobulin (Coombs) test (if known)
	Presence of haemolytic disease (other than blood group antagonism)
	Presence of birth asphyxia: Apgar score <5 at 5 min or pH <7.0 in umbilical cord blood
	Suspicion of sepsis
	Neonate being ill or drowsy
Other characteristics	Siblings who experienced neonatal hyperbilirubinaemia (and cause of hyperbilirubinaemia, if known)

The maternity care professionals will record several measurements during PCBC stay. These measurements are noted in table 3. All data will be recorded in standardised case report forms. The study team, the study monitor, and (inter)national supervisory authorities will have access to the data and the final dataset.

**Table 3 T3:** Daily measurements in PCBC

Daily measurements	
Control period	Skin colour: pink, slightly yellow, moderately yellow, quite yellow, very yellow
	Weight (in grams)
	Risk factors for hyperbilirubinaemia (if present)
	TSB values with date and time of measurement (if relevant)
	Decisions made based on TSB (if relevant)
Period with TcB screening (extra measurements in addition to control period)	TcB values measured at forehead and sternum together with date and time of measurement (once a day or two times if indicated)
Phototherapy in PCBC (extra measurements in addition to control period)	Start and end date and time of phototherapy
	Decisions made by the affiliated paediatrician regarding phototherapy

PCBC, primary care birth centres; TcB, transcutaneous bilirubinometry; TSB, total serum bilirubin.

A questionnaire for the parents/caregivers to evaluate their experience will be sent by email 14 days after the birth of the neonate. This questionnaire will assess parental satisfaction, burdensomeness of interventions for the neonate and experienced competence of maternity care professionals. If parents do not have access to the internet or do not respond to the questionnaire by email, they will be approached by regular mail or by phone. The community midwife and/or the general practitioner will be approached if parents do not respond at all. Both after the control and after each intervention period, maternity care personnel will be invited to complete a questionnaire about their experiences regarding the daily practice of hyperbilirubinaemia assessment and treatment during these periods (eg, facilitators and barriers for implementation, sense of competence regarding applying the new interventions, integrating the new interventions in routine care, and the content of the training regarding the new interventions).

